### 4.1. Data Management

Data will be recorded on the case report form at each site. A bespoke online data storage system will be developed for the central processing of the recorded data. Data entry will be conducted by at least two assessors to minimize data entry errors. Study conduct monitoring will be performed by a dedicated committee from the participating site on an annual basis. Recorded data will only be accessible by authorized personnel.

### 4.2. Data Analysis

All statistical analyses will be performed in IBM SPSS version 21 software (SPSS Inc., Chicago, IL, USA). Descriptive statistics will be conducted to describe the sample population. The demographic characteristics and baseline results for the primary and secondary outcome measures will be analyzed using analysis of variance (ANOVA) or Chi-square test for categorical data. A mixed-effect model analysis will be adopted to compare changes in all of the outcome measures between groups at the completion of the intervention and at the 3- and 6-month follow-ups. The mixed-effect model analysis will include treatment, time, and centre as fixed effects, and the participants will be included as the random effect. Changes in the outcome measures will be adjusted for age, sex, centre, and time. The level of statistical significance will be set at *p* < 0.05. Cohen’s d will be calculated to measure the effect size of the difference for every comparison. The effect size will be interpreted as follows: 0.2—small effect size; 0.5—medium effect size; and 0.8—large effect size. Stratification analysis will be conducted to explore the potential effect difference between centres. There are no planned interim analyses or stopping rules, as the power calculation has accounted for loss to follow-up. In the event of missing data during the follow-up period, the modified intention to treat principle will be followed with the last observation carried forward method. 

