The primary aim of the present study is to investigate the effect of interlimb-coordinated intervention on gait and motor function in patients with stroke at the acute stage. It is hypothesized that acute stroke patients who receive interlimb-coordinated intervention will significantly improve gait and upper-limb motor function. These improvements would be significantly higher than those who receive conventional therapy immediately after the 2 weeks of intervention and at the 3- and 6-month follow-up periods. The secondary aim is to investigate the neural plasticity changes that are induced by interlimb coordinated intervention after 2 weeks of intervention and at the 3- and 6-month follow-up periods. It is also hypothesized that the participants who undergo interlimb-coordinated intervention would have stronger cortical activation at rest and during gait and a shorter neural processing time to initiate a motor task than the participants in the control group immediately after intervention and at the 3- and 6-month follow-up periods. 

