### 2.7. Outcome Measures

#### 2.7.1. Primary Outcome Measure

The primary outcome measure is gait speed, which will be assessed by the 10 m walk test. 

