#### 2.7.2. Secondary Outcome Measure

All outcome measures will be recorded at baseline, post-intervention, and at 3 and 6 months post-intervention. Table 1 presents a brief description of each of the secondary outcome measures that will be recorded at all participating centres. The outcome measures of the 10 m walk test, Fugl–Meyer Assessment, and Action Research Arm Test are the recommended outcome measures by expert consensus from national societies in the United States for body function and activity [39]. The Berg Balance Scale (BBS) was also reported to be a tool that is valid, reliable, and sensitive to change in post-stroke balance impairment assessments despite the potential concern of the ceiling and flooring effect [40]. The timed-up and go test (TUG) was initially developed to identify balance impairment [41] and has been reported as a reliable, valid, and easy-to-administer clinical tool that can be used to assess mobility and balance [42]. Both the BBS [43] and TUG [44] are strong fall predictors. The Instrumental Activities of Daily Living has also been reported as an international gold standard despite its limitations and biases [45].

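### The listed mixed-model terms contain no treatment-by-time interaction, so the model as written gives one visit-averaged effect, not the promised comparisons at three visits

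*Protocol article*

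**What the plan says.** The primary outcome is gait speed on the 10 m walk test (section 2.7.1), with no single primary time point named. Section 2.7.2 gives four occasions: "All outcome measures will be recorded at baseline, post-intervention, and at 3 and 6 months post-intervention".

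The Introduction hypothesises improvements "significantly higher than those who receive conventional therapy immediately after the 2 weeks of intervention and at the 3- and 6-month follow-up periods".

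Section 4.2 gives the mixed model that same task, to "compare changes in all of the outcome measures between groups at the completion of the intervention and at the 3- and 6-month follow-ups". The next sentence lists the terms: "The mixed-effect model analysis will include treatment, time, and centre as fixed effects, and the participants will be included as the random effect". A further sentence gives the covariates: "Changes in the outcome measures will be adjusted for age, sex, centre, and time". No interaction between treatment and time is mentioned there or elsewhere in the article.

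The sample size (section 2.12) uses G*Power's repeated-measures procedure for between factors: means 0.69 and 0.39 m/s, SD 0.75, effect size 0.2, 95% power, 206 participants before allowance for missing data.

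**The concern.** The sentence stating the model's purpose and the sentence listing its terms do not fit together. With treatment and time entered only as main effects, the group difference is constrained to be the same at every visit, and the output is a single treatment coefficient. The hypothesis concerns three separate times, and the Discussion says that the follow-up data will show whether the intervention is superior in the longer term. One averaged coefficient cannot tell a gain that is lost by 6 months from one that lasts or one that appears late.

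This is the only between-group efficacy model described, and it serves the primary and the secondary outcomes. If the interaction is added only after the data have been seen, the per-visit comparisons become post hoc choices.

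**Working it through.** **Inputs.** From section 2.12: difference 0.30 m/s, SD 0.75, 206 participants (103 per arm). From section 2.7.2: four occasions. From section 4.2: alpha 0.05. The correlation between visits, ρ, is not stated; 0.5 is assumed, with a range of 0.3 to 0.7. Further assumptions: equal SD and equal correlation at all visits, complete data, no precision gain from covariates unless stated.

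**1. The plan's own figure.** Effect size f = (0.30/2)/0.75 = 0.20. For a between-factor test over m visits, λ = f²·N·m / [1 + (m − 1)ρ], with 1 and N − 2 df. With m = 4 and ρ = 0.5, λ = 0.04 × 206 × 4 / 2.5 = 13.18 and power is 0.951. The smallest N is 206, as stated. Among m = 1 to 4 and ρ = 0.3, 0.5 and 0.7, only this combination gives 206. The powered test is therefore a group main effect averaged over visits.

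**2. What the listed terms estimate.** Let δ(t) be the true group difference at visit t. With balanced data, the treatment coefficient of an additive random-intercept model is the plain mean of the δ(t). The plan's last-observation-carried-forward rule fills missing follow-up values and so moves the data towards that balanced case.

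| True difference at end of intervention, 3 and 6 months (m/s) | Response is change, three visits | Response is gait speed, four visits including baseline |
|---|---|---|
| 0.30, 0.30, 0.30 | 0.30 | (0 + 0.90)/4 = 0.225 |
| 0.30, 0.15, 0 | 0.45/3 = 0.15 | 0.45/4 = 0.1125 |
| 0, 0.15, 0.30 | 0.45/3 = 0.15 | 0.45/4 = 0.1125 |

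The last two rows cannot be told apart on either reading.

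A simulated data set (2000 per arm, four visits, constant 0.30 after baseline) agrees. The additive model gave 0.23. Adding treatment by time gave 0.32, 0.28 and 0.28 for the three follow-up visits.

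**3. Power of the averaged effect when the true effect is a constant 0.30 m/s.**

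- *Change as response.* The variance of the mean of three changes is 0.75²·[(1 + 2ρ)/3 + 1 − 2ρ]. At ρ = 0.5 this is 0.5625 × 0.667 = 0.375. The noncentrality is 0.30/√(2 × 0.375/103) = 3.52, and power is about 94%. It is 84% at ρ = 0.3 and above 99% at ρ = 0.7.
- *Baseline among the responses.* f = (0.225/2)/0.75 = 0.15, so λ = 0.0225 × 206 × 4 / 2.5 = 7.42 and power is about 77%. It is 87% at ρ = 0.3 and 68% at ρ = 0.7.

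**4. Power of a contrast at one visit, 0.30 m/s, 103 per arm.**

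- *Change from baseline.* Variance 2 × 0.75² × (1 − ρ) = 0.5625 at ρ = 0.5. The noncentrality is 0.30/√(2 × 0.5625/103) = 2.87, and power is about 82%. It is 68% at ρ = 0.3 and 96% at ρ = 0.7.
- *Adjusted for baseline.* Variance 0.75² × (1 − ρ²) = 0.422 at ρ = 0.5. The noncentrality is 0.30/√(2 × 0.422/103) = 3.31, and power is about 91%.

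**The case against.** The list of terms need not be closed. The sentence after it adds age and sex, a journal article condenses, and naming factors without their interaction is a common shorthand. The per-visit wording and the plan to compute Cohen's d for every comparison both suggest that visit-specific contrasts are intended. This stands as a reason for caution about what the investigators will do. It does not repair the text: the article chose to specify the model, and the term that answers its hypothesis is the one absent. Separate models for each visit are a poor alternative reading, since time would then be constant and a participant random effect would have no repeated observations behind it.

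A reader might also infer that the analysis dilutes the treatment effect by a quarter and that true power is 77%, not 95%. The documents do not support that as the main reading. Section 4.2 twice names changes as the quantity analysed and lists only post-baseline times. On that reading there is no dilution. The four-measurement setting that reproduces 206 is not stated in section 2.12, and a sample-size setting does not define the response in section 4.2.

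Nor does it follow that the efficacy comparison is invalid. An average post-baseline effect is a proper randomised comparison and is the kind of effect that the power calculation addresses. What is lost is its course over time.

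**Conclusion.** The point holds as a mismatch between the stated purpose of the model and its stated terms. As written, the model gives one treatment effect averaged over visits and cannot test the hypothesis at each of the three times: a fading and an emerging effect both come out at 0.15 m/s on change scores. These two patterns are illustrations, not predictions.

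With change as the response, the average is valid and undiluted, and its power at 0.30 m/s is close to that planned (about 94% at ρ = 0.5; 84% to above 99% over 0.3 to 0.7). Dilution to 0.225 m/s, with power of about 77% (87% at ρ = 0.3, 68% at ρ = 0.7), is conditional on baseline being one of the modelled responses. All powers rest on the plan's SD of 0.75 and on an assumed correlation. The specification should be corrected before the data are analysed.

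**What to change.** In section 4.2:

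1. Add treatment by visit, with visit categorical. Over three post-baseline visits this costs two more parameters.
2. State that the response is the post-baseline value or the change from baseline, and that baseline itself is not a response.
3. Include the baseline value, already collected, as a covariate alongside centre, age and sex.
4. Report the treatment contrast at each of the three visits from the interaction.

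No new data are needed. The price is power: a single-visit contrast is weaker than the averaged test. For 0.30 m/s in change it has about 82% at ρ = 0.5 (68% to 96% over 0.3 to 0.7), or about 91% at 0.5 with baseline adjustment. Section 2.12 should therefore say that its 95% applies to the visit-averaged test. Whether to name one visit as primary is a separate decision for the sponsor, because it changes the test that was powered.

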### 2.12. Sample Size

Sample size calculation will be based on the primary outcome measures of gait speed. An increase in gait speed of 0.16 m/s has been stated as the minimal clinically significant difference in the first 60 days of stroke occurrence [54] that correlating with a meaningful improvement in disability level post intervention. The study will consider 0.3 m/s for power calculation since other study-reported changes below this value are likely to be measurement errors [55].

The sample size was determined using the sample size calculator G*Power. The calculation model is based on the F test family, the statistical “ANOVA: Repeated measures, between factors” test and the “A priori: Compute required sample size–given alpha power, and the effect size” as the power analysis type. Power calculation was based on a mean difference of 0.3 (mean of group 1 = 0.69; mean of group 2 = 0.39) and the standard deviance of each group of 0.75 with a total sample population of 60. A total of 206 participants (103 in each group) is required to provide 95% power and an effect size of 0.2. Taking a 10% missing rate into consideration, a final sample size of 226 participants (113 in each group) was determined. 

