## 5. Discussion

Several clinical guidelines propose that active rehabilitation is to be provided within 24–48 h of stroke occurrence [57], as the most considerable amount of the recovery was reported to take place in the first month following stroke [58]. Available evidence supports the benefits of early rehabilitation intervention on motor recovery, but convincing evidence for an early interlimb coordinated intervention is lacking. Thus, this study will provide evidence on the feasibility and efficacy of interlimb coordinated movement as part of an early intervention program for gait and motor function improvement. The medium long-term efficacy of the interlimb coordinated intervention will also be assessed in this study. Several Cochrane reviews regarding the efficacy of other interventions on motor function recovery seldom report data beyond the initial discharge period [59] or has followed up beyond the three [60] or six month periods [61]. As motor function capacities evolve the most during the first month of stroke onset [62], it is anticipated that intervention provided during the acute stage of stroke has better clinical outcomes when compared to interventions that are provided at later stroke stages. Therefore, 3- and 6-month post-intervention follow-up data will increase the understanding of whether interlimb coordinated intervention is superior to conventional therapy in the longer term. 

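### A participant random effect alone assumes equal variance and equal correlation across unequally spaced visits; if correlation with baseline decays, the 6-month change comparison has too small a standard error

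*Protocol article*

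**What the plan says.** Section 4.2 (Data Analysis) of the protocol article gives the model in two parts. For the fixed part: "The mixed-effect model analysis will include treatment, time, and centre as fixed effects". For the random part: "the participants will be included as the random effect". It adds adjustment for age, sex, centre and time. No random slope, residual covariance structure or treatment-by-time term is listed.

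The purpose of the model is to "compare changes in all of the outcome measures between groups at the completion of the intervention and at the 3- and 6-month follow-ups". The visits come from section 2.7.2: "All outcome measures will be recorded at baseline, post-intervention, and at 3 and 6 months post-intervention". With a 2-week intervention, these fall at about 0, 0.5, 3.5 and 6.5 months from baseline. On the test level, section 4.2 says: "The level of statistical significance will be set at *p* < 0.05".

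**The concern.** A random intercept with independent, equal-variance residuals implies compound symmetry: the same variance at every visit, and the same correlation between visits two weeks apart as between visits six months apart. Patients enter within the first month of stroke, when function is moving quickly, and the visits are far from equally spaced. Equal correlation is hard to defend in that setting.

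The planned results are changes from baseline compared between groups at three separate times. A compound-symmetry fit gives all three changes the same standard error, whatever their true variability. If correlation with baseline weakens over time, the 6-month change is the most variable of the three and its pooled standard error is too small. The 6-month comparison is also one on which the longer-term superiority claim in the Discussion rests, so false positives would do most harm there.

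**Working it through.** **The plan's own figure.** Section 2.12 says: "Power calculation was based on a mean difference of 0.3". With the stated SD of 0.75, f = (0.3/2)/0.75 = 0.2. For the G*Power procedure named there, the noncentrality is λ = f²·N·m/(1 + (m − 1)ρ), with 1 and N − 2 degrees of freedom. Taking m = 4 visits and ρ = 0.5 (neither is stated), N = 206 gives λ = 0.04 × 206 × 4/2.5 = 13.18 and power 95.1%. N = 204 gives 94.9%. The stated 206 is therefore reproduced, by a formula that uses one common correlation. It tells us nothing about the real correlations.

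**Inputs for the check.** The random part, the contrasts and the visit times are from sections 4.2 and 2.7.2. SD 0.75 and 103 per group are from section 2.12. The test is taken as two-sided at 5%. All between-visit correlations, and any SD that varies by visit, are assumptions. Data are taken as complete, with separate group-by-visit means.

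**Formulas.** With balanced data the random-intercept fit converges to compound symmetry with the mean variance s² and mean covariance c of the true matrix.

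- Ratio of model SE to true SE for change from baseline at visit t: √[2(s² − c)/(v₀ + v_t − 2c₀t)]. With equal SDs this is √[(1 − mean correlation)/(1 − correlation of baseline with t)].
- Actual type I error: 2[1 − Φ(1.96 × ratio)].

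**One case in full.** Assume correlations with baseline of 0.85, 0.70 and 0.60. Assume 0.80 for 2 weeks with 3 months, 0.70 for 2 weeks with 6 months, and 0.90 for 3 with 6 months. The mean correlation is 4.55/6 = 0.758.

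- 2 weeks: √(0.2417/0.15) = 1.27; type I error 1.3%.
- 3 months: √(0.2417/0.30) = 0.90; type I error 7.9%.
- 6 months: √(0.2417/0.40) = 0.78; type I error 12.8%. In m/s, the model SE is 0.073 against a true 0.094.

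**Range, equal SDs at all visits**

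| Assumed true pattern | Correlation with baseline | SE ratio 2 wk / 3 m / 6 m | Type I error at 6 m |
|---|---|---|---|
| Case above | 0.85, 0.70, 0.60 | 1.27 / 0.90 / 0.78 | 12.8% |
| Milder decay (other pairs 0.80, 0.75, 0.85) | 0.80, 0.70, 0.65 | 1.10 / 0.90 / 0.83 | 10.3% |
| By lag | 0.80, 0.70, 0.60 | 1.16 / 0.94 / 0.82 | 11.0% |
| AR(1), 0.8 per visit | 0.80, 0.64, 0.51 | 1.23 / 0.92 / 0.79 | 12.4% |
| Exponential, 0.9 per month | 0.95, 0.69, 0.50 | 2.46 / 1.00 / 0.79 | 12.1% |
| Exponential, 0.8 per month | 0.89, 0.46, 0.23 | 2.22 / 0.98 / 0.83 | 10.6% |
| Early change, then plateau (other pairs 0.80, 0.75, 0.92) | 0.70, 0.55, 0.50 | 0.99 / 0.81 / 0.77 | 13.1% |
| True compound symmetry | 0.50, 0.50, 0.50 | 1.00 / 1.00 / 1.00 | 5.0% |

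Wherever correlation decays, the 6-month SE is 17% to 23% too small. The 2-week ratio runs from 0.99 to 2.46.

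**Cases that limit the point**

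- *Falling SD, flat correlation.* With SDs of 0.80, 0.75, 0.60 and 0.50 and correlation 0.5 throughout, the change ratios are 0.89 / 0.95 / 0.98. The early SE is then the one too small, and the 6-month SE is nearly right.
- *Falling SD, first-row correlations.* The change ratios are 1.16 / 0.87 / 0.78, so the 6-month result stays.
- *Group difference at a visit without baseline correction.* The ratio is 1.00 at every visit when SDs are equal. It is 0.90 / 1.12 / 1.35 with the falling SDs, which reverses the direction.
- *One treatment effect averaged over the post-baseline visits.* The ratio is 1.00 in every case.
- *Change scores as the dependent variable* (another reading of the text). The first-row correlations give 1.37 / 0.97 / 0.84 and type I error 0.7% / 5.7% / 9.9%, in the same direction.

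**The case against.** The strongest objection is that the article never says intercept only, nor that residuals are independent. The software can fit a residual structure beside a participant random effect, and such detail is commonly left to an analysis plan that is not shown here. This stands in part. It is why the point is put as conditional on the natural reading, and why one cannot say that the plan forces equal correlation. It does not dispose of the point, because the article states a model, and that model run as written is a random intercept.

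A reader might also infer that standard errors will be too large early and too small late, and that the document itself shows this when it says: "As motor function capacities evolve the most during the first month of stroke onset". The documents do not support that reading. The sentence concerns how much function changes, not how visits correlate. A pattern of rapid early change and then stability leaves the 2-week standard error about right (0.99), although the 6-month one is still too small. No correlation or visit-specific SD is given, so neither direction is established as fact.

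Third, the listed fixed effects contain no treatment-by-time term. Taken literally, the model yields one treatment effect, whose standard error is correct under compound symmetry with complete data. That is fair, but the stated aim is a comparison at each of three times, and that cannot be met without the interaction.

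Last, the check assumes complete data, while section 4.2 prescribes last observation carried forward. That would add artificial correlation between late visits, and its effect is not quantified here.

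**Conclusion.** The concern holds in conditional form. On the natural reading, the stated random part assumes equal variances and equal correlations over four unequally spaced visits in early stroke recovery, and that assumption is doubtful.

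If correlation with baseline decays and SDs are roughly constant, the 6-month change comparison has a standard error about 17% to 23% too small and a type I error of roughly 10% to 13% against the nominal 5%. The 2-week comparison may be conservative or about right. There is no error under true compound symmetry or for a single averaged treatment effect, and uncorrected visit-level differences can be unaffected or go the other way. The result rests on assumed correlations, complete data and a treatment-by-time term that the article does not list. The change is worth making because it is cheap and protects the 6-month conclusion; an error in the trial's results has not been demonstrated.

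**What to change.** In section 4.2, add the treatment-by-time term that the visit-specific comparisons require. Replace the participant random effect with an unstructured covariance over the scheduled visits, fitted by REML with Satterthwaite degrees of freedom. Name in advance a simpler structure to use if the model does not converge, for example a heterogeneous Toeplitz form. If a random intercept with a residual structure was intended all along, say so and name the structure.

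The cost is a few lines of model specification in the stated software. Four visits give 10 covariance parameters against 2 for the random intercept. With 226 patients the loss of precision is negligible, even if equal correlation turns out to be true. No new data and no design change are needed.

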### 2.5. Randomization

Eligible participants will be randomly assigned to either the experimental or the control group at a ratio of 1:1 without stratification. A statistical expert from the Faculty of Medical Statistics and Epidemiology, Sun Yat-sen University, computed the random allocation sequence. The sequence will be uploaded onto a central operating system. Research team members will access the system at the time of participant enrolment by dialing the central phone number to obtain the allocation. The operating system will provide the numbers of 001 and 002, which correspond to the intervention group and control group, respectively. Each participant will be assigned a unique identification number to maintain confidentiality. 

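### The primary model adjusts change in gait speed for age, sex, centre and time but not for baseline gait speed, which gives away precision at no saving

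*Protocol article*

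**What the plan says.** The primary outcome is gait speed on the 10 m walk test (section 2.7.1). Section 2.7.2 states: "All outcome measures will be recorded at baseline, post-intervention, and at 3 and 6 months post-intervention". Table 2 confirms a baseline gait-speed assessment.

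The analysis is in section 4.2. The quantity compared is the change: "A mixed-effect model analysis will be adopted to compare changes in all of the outcome measures between groups at the completion of the intervention", and again at the 3- and 6-month follow-ups. The model terms are then listed: "The mixed-effect model analysis will include treatment, time, and centre as fixed effects, and the participants will be included as the random effect". The adjustment set follows: "Changes in the outcome measures will be adjusted for age, sex, centre, and time".

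Baseline outcome values appear in section 4.2 in one other role, a between-group comparison at baseline, which does not adjust the treatment effect. Section 2.5 says participants are "randomly assigned to either the experimental or the control group at a ratio of 1:1 without stratification". Nowhere does the article add a baseline covariate or constrain the baseline means to be equal across arms.

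**The concern.** Subtracting the baseline value assumes that follow-up speed rises one-for-one with baseline speed. With equal SDs at the two visits the regression slope is r, which is below 1. A plain change score therefore over-corrects: an arm that starts faster by chance is expected to show a smaller gain. Fitting baseline as a covariate estimates the slope instead of fixing it at 1.

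The participant random effect does not repair this. The same baseline value, with its measurement error, is subtracted from all three of a participant's changes, so averaging over visits does not remove it.

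At stake are the width of the confidence interval and the power for the primary outcome, and how far the estimate depends on a chance difference in starting speed. Unstratified allocation balances baseline speed in expectation only and does nothing to limit the imbalance that actually occurs. Because the covariates are spelled out, an analysis plan written to match would carry the omission forward.

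**Working it through.** **Inputs from section 2.12:** mean difference 0.3 m/s, SD 0.75 per group, effect size 0.2, 95% power, 206 evaluable participants (103 per arm). **From section 2.7.2:** four measurements (m = 4). **From section 4.2:** significance level 0.05, taken as two-sided. **Assumed:** SD 0.75 applies to gait speed at every visit, with one common correlation r between visits. The article gives no r.

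**1. Reproduce the plan's figure.** The effect size is f = 0.3 / (2 × 0.75) = 0.2. For the between-factors repeated-measures F test, λ = f²·N·m / (1 + (m−1)r). With N = 206, m = 4 and r = 0.5, λ = 0.04 × 206 × 4 / 2.5 = 13.18 on 1 and 204 degrees of freedom, which gives power 95.1%. N = 204 gives 94.9%. So 206 reproduces at r = 0.5, and that value is inferred, not stated.

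**2. Variance of the treatment contrast at one visit, in units of SD².**
- Change score: 2(1−r)
- Baseline as covariate: 1−r²
- Ratio: (1−r²) / [2(1−r)] = (1+r)/2, below 1 for every r < 1

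Regressing the change on baseline gives the same treatment estimate as regressing the follow-up value on baseline, so either form of the model will do.

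**3. Power at one visit**, two-sided t test, 103 per arm, difference 0.3 m/s, standard error 0.75 × √variance × √(2/103):

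| r | Variance, change | Variance, adjusted | Reduction | Power, change | Power, adjusted |
|---|---|---|---|---|---|
| 0.3 | 1.40 | 0.91 | 35% | 67.5% | 85.0% |
| 0.5 | 1.00 | 0.75 | 25% | 81.5% | 91.0% |
| 0.6 | 0.80 | 0.64 | 20% | 89.1% | 94.6% |
| 0.7 | 0.60 | 0.51 | 15% | 95.8% | 97.9% |
| 0.8 | 0.40 | 0.36 | 10% | 99.5% | 99.7% |

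A simulation of 4,000 trials at r = 0.5 gave a variance ratio of 0.747, against 0.75 from the formula. For 95% power at one visit and r = 0.5, the normal approximation n = 2(1.960 + 1.645)² × variance × 0.75² / 0.3² gives 163 per arm with change scores and 122 with adjustment.

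**4. Mean of the three follow-ups.** The variance is (1+2r)/3 + 1 − 2r for change and (1+2r)/3 − r² with adjustment. At r = 0.5 these are 0.667 and 0.417, a 37.5% reduction. Power goes from about 94% to about 99%. The proportional loss is larger than at one visit because the baseline value is common to all three changes.

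**5. Chance imbalance.** The standard error of the baseline difference is 0.75 × √(2/103) = 0.105 m/s, so an imbalance of 0.10 m/s is an ordinary result. Given that imbalance, the change-score estimate shifts by (r−1) × 0.10 = −0.05 m/s at r = 0.5. That is 0.05/0.3 = 17% of the planned difference, and 0.05/0.16 = 31% of the minimal clinically significant difference cited in section 2.12. At r = 0.8 the shift is −0.02 m/s.

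**The case against.** Several points on the other side have force.

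- **The correlation is inferred.** Section 2.12 states neither r nor the number of measurements used. By the same formula, about 0.44 with three measurements or 0.25 with two would also give 206. Even if 0.5 was used, it is a planning input and not evidence about these patients. This stands, and it is why a range is shown. If baseline speed predicts follow-up speed strongly, r is high and the loss is only 5% of variance at 0.9.
- **Single-visit power is not what the trial was sized on.** The sizing uses a test over repeated measurements, and for the mean of three follow-ups the change-score analysis already has about 94% power at r = 0.5. This is also true. However, the hypotheses in section 1 and the comparisons in section 4.2 are made at each of three time points, so single-visit precision matters too, and adjustment still helps the averaged contrast.
- **The change-score comparison is unbiased over randomisation.** The 0.05 m/s shift is conditional on the imbalance that occurs, and over repeated trials it is part of the same extra variance, not a second harm. This is right, and lack of stratification is not itself a defect here.
- **The response may be the repeated values, with baseline as a time level.** Section 4.2 does not settle this. An unconstrained treatment-by-time contrast would equal the change-score comparison and lose the same precision. Only a model with equal baseline means would recover it, and the text does not state one.
- **A condensed article may leave this to an analysis plan.** That would be a good answer if the covariates were left open. They are listed, and baseline is not among them.

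**Conclusion.** The concern holds. Section 4.2 makes an explicit choice that is less precise than the baseline-adjusted analysis for any r below 1. The cost is 25% of the variance at one visit if r = 0.5, 15% at 0.7 and 10% at 0.8. In single-visit power that is 9.5 percentage points at 0.5 (91.0 − 81.5), about 2 at 0.7 (97.9 − 95.8) and almost nothing at 0.8. These figures assume SD 0.75 and a common correlation at all visits.

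The omission does not make the planned analysis invalid, nor the stated 206 wrong. It should be corrected because the gain needs no new data and makes the primary result less dependent on a chance difference in starting speed.

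**What to change.** In section 4.2, add the baseline value of the same outcome as a covariate, for gait speed and for each secondary outcome, alongside age, sex and centre. The response can be the follow-up value or the change. An equivalent route is to keep baseline as a time level in the mixed model and state that the baseline means are constrained equal across arms.

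The cost is one model term per outcome. No additional data, visits or participants are needed, and 206 can stand. The change should be dated before unblinding and before the planned baseline comparison is seen, so that the adjustment cannot appear to have been prompted by an observed imbalance.
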